### Hypothesis

We hypothesize that targeting clinical tissue perfusion (the TTP arm) will decrease the use and untoward effects of vasopressors, and result in more days alive in 30 days with normal arterial blood lactate (first value of <2 mmol/L) *and* without any inotropic or vasopressor agent – compared to standard clinical care with preference of macrocirculatory targets (the MCG arm).

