### Statistical methods

The study flowchart is included as Fig. 1. A Mann-Whitney test for differences in continuous outcomes including the primary outcome measure, and Fisher’s exact test for dichotomous variables will be done as a primary analysis. A sensitivity analysis in subgroups of patients with and without previous hypertension will be performed. The components of the primary outcome measure (time to normalization of lactate, time to stopping of all vasoactive drugs, and day-30 mortality) are all included among secondary outcomes. In all tests a *p* value of less than 0.05 will be considered statistically significant. If missing data are >5 %, multiple imputations will be performed. A detailed statistical analysis plan is provided in Appendix 5.

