### Perspectives

Septic shock affects millions of patients worldwide annually. The results of study will – in any case – have a major influence on the clinical management/international guidelines regarding treatment of septic shock. If supporting our hypothesis of the beneficial effects of TTP, the current recommendations will have to be changed leading to major scientific and societal impacts on heath and health care costs. In case MCG proves to be better, the study results will for the first time confirm the widely recommended minimum MAP level. Given that several different pathophysiological pathways are probably in interaction and may only partly explain the clinical course of the disease, the potential strength of measuring several biomarkers/mitochondrial function/gene expression and protein synthesis in the sub-studies of this phase II study, will give us the opportunity to compare their relative importance and predictive power with regard to organ dysfunction.

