## Appendix 5 A detailed study statistical analysis plan

The primary analysis of the primary outcome (as well as secondary outcomes b, c, d, e, f, h, i, and j) will be an unadjusted Mann-Whitney test. As a sensitivity analysis the *p* values will be recalculated using permutations within groups defined by site and the presence/absence of hypertension. This test is a non-parametric version of an ANOVA adjusted for site and presence/absence of hypertension. A total of 100,000 permutations will be conducted for each test. The effect sizes will be quantified by direct comparisons of the raw means between groups. Confidence intervals will determined by non-parametric bootstrapping to accommodate the highly non-normal distribution of the outcomes.

The secondary endpoint “a” will be assessed by a Cox model treating death before normalization of lactate as a competing event. The Cox model will be adjusted for site and presence/absence of hypertension. The effect size will be quantified using the adjusted hazard ratio.

The secondary outcome “g” will be assessed using Fisher’s exact test. Effect sizes will be analyzed using crude proportions along with standard normality approximation-based confidence intervals.

The exploratory endpoint (90-day survival) will be assessed using Fisher’s exact test. Effect sizes will be quantified using odds ratios from a logistic regression adjusted for site and the presence of hypertension. As a sensitivity analysis a Cox model of time to death will also be employed. The Cox model will be adjusted for site and the presence/absence of hypertension. Here, the effect size will be quantified using the adjusted hazard ratio. The assumption of proportional hazards will be assessed using Schoenfeld residuals. Finally, Kaplan-Meier plots will be produced.

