If any of the tests presented above must be based on data with more than 5 % missing multiple imputation will be employed. If just one test needs to be based on multiple imputation all tests will be conducted both as complete case analysis and multiple imputation. However, only for tests based on data with more than 5 % missing will the multiple imputation approach constitute the primary analysis. The multiple imputation will be conducted in R using the mice package and the recommendation in accordance with recommendations in the documentation of this package. All outcome variables (secondary and primary), sex, and age as well as stratification and treatment variables will be included in the multiple imputations procedure.

In all tests a *p* value of less than 0.05 will be considered statistically significant. It is noted that as the adaptive sample size recalculation is not depended on a particular value of the treatment effect at the time of recalculation, there is accordingly no need to adjust the significance level to take a possible adjustment of sample size into account. All analyses will be conducted in the statistical software package R. The full statistical analysis will be conducted blinded to actual treatment allocation and a full blinded statistical report produced. Of note, un-blinding will first happen after the full statistical report has been finalized.

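### Every test is called significant at p<0.05, including ten secondary outcomes, with no order or multiplicity rule among them and no link to the primary result

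*Protocol article*

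**What the plan says.** Statistical methods and Appendix 5 give the same rule. In Appendix 5 it reads: "In all tests a *p* value of less than 0.05 will be considered statistically significant".

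Appendix 5 assigns a test to each of the ten secondary outcomes, lettered in the order of the Secondary outcome measures list:

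- Eight are compared by rank test: "secondary outcomes b, c, d, e, f, h, i, and j) will be an unadjusted Mann-Whitney test".
- Outcome a, time to normal lactate, "will be assessed by a Cox model treating death before normalization of lactate as a competing event".
- Outcome g, new acute kidney injury, has Fisher's exact test.

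Outcome j is itself a group: seven named reactions plus totals of serious adverse reactions.

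The Hypothesis section states that the intervention "will decrease the use and untoward effects of vasopressors, and result in more days alive in 30 days with normal arterial blood lactate". The first half of that clause corresponds to secondary outcomes i (norepinephrine given to day 5) and j; the second half is the primary outcome.

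The only discussion of adjusting the significance level, in Appendix 5, concerns the blinded sample-size recalculation.

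**The concern.** This is a rule that the document states, not a gap that a fuller plan might fill. Statistical methods refers to Appendix 5 as the detailed analysis plan, and that appendix repeats the rule without qualification. Read literally, a neutral primary result may be accompanied by one or more secondary outcomes that the plan itself declares significant, in either direction (less organ support, say, or more kidney injury).

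Because the hypothesis combines the primary outcome with vasopressor use and untoward effects, a significant i or j could be presented as confirming part of it. Outcome i needs particular care. The arms have different arterial pressure targets, so less norepinephrine may show only that the strategies were separated. The Perspectives section also sets high expectations: "The results of study will – in any case – have a major influence on the clinical management/international guidelines regarding treatment of septic shock". What is at stake is how far secondary results may be claimed, not the validity of the primary test.

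**Working it through.** **Inputs from the document.** Significance level 0.05 in all tests (Statistical methods; Appendix 5); ten secondary outcomes (Secondary outcome measures); at least 200 patients (Abstract); 25 % mortality, 18 h change among survivors, log-normal time with mean 70 h and SD 30, Mann-Whitney test (Sample size and power).

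**Assumptions.** Two-sided tests, 1:1 allocation, and all correlations between outcomes. The document states none of these.

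**Step 1: the plan's own figure.** The plan gives no error rate for the secondary outcomes. Its primary power figure was reproduced first, to fix the meaning of 0.05. With 10,000 simulated trials, Table 1's N = 194 gives 78.8 % power and N = 200 gives 80.0 %, two-sided. One-sided testing at 0.05 would give 86 to 88 %. So the stated 80 % fits a two-sided 5 % test of the primary outcome.

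**Step 2: independent tests, no true effect.** P(at least one p<0.05) = 1 − (1 − 0.05)^k.

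- k = 10: 1 − 0.95^10 = 1 − 0.599 = 0.401, or 40 %.
- The expected number of false significant results is 10 × 0.05 = 0.5, whatever the correlation.

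**Step 3: correlated tests.** Ten standard normal statistics with common correlation ρ, each rejected when |Z| > 1.96, 200,000 draws:

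| ρ | 0 | 0.2 | 0.3 | 0.5 | 0.6 | 0.7 | 0.8 | 0.9 |
|---|---|---|---|---|---|---|---|---|
| P(at least one) | 40.1 % | 37.7 % | 35.2 % | 28.6 % | 25.1 % | 21.4 % | 17.3 % | 12.8 % |

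**Step 4: simulation at outcome level.** Equal correlation is a simplification, because the outcomes overlap in a specific way: the days-alive measures share the same deaths, and f combines what d and e measure. Null trials were therefore simulated with N = 200, 25 % mortality, and all ten outcomes linked through death and a shared severity factor (4,000 trials per setting; durations and event rates assumed).

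| Severity correlation | 0 | 0.2 | 0.4 | 0.6 | 0.8 | 0.95 |
|---|---|---|---|---|---|---|
| Ten outcomes | 31.3 % | 29.6 % | 26.2 % | 22.1 % | 19.7 % | 15.9 % |
| Plus eight Fisher tests on reactions | 38.4 % | 36.3 % | 32.5 % | 28.4 % | 24.7 % | 20.0 % |

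The second row adds the seven named reactions and patients with any reaction as separate tests. Appendix 5 lists no such tests, so that row shows only what would follow if they were done.

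**The case against.** The strongest reply is that the article already ranks its outcomes. It has one primary outcome, a secondary tier and an exploratory tier. Type 1 error, power and sample size attach to the primary outcome only, and the difference said to be tested is the difference in that outcome. Ethical considerations ties the phase III decision to feasibility, separation and the primary endpoint in a phase II trial. Appendix 5 plans effect sizes for the secondary outcomes, with confidence intervals for those tested by Mann-Whitney and for g. The vasopressor wording in the hypothesis can be read as the mechanism behind the primary outcome. The sentence in Perspectives does not mention secondary outcomes.

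Most of this stands, and it rules out several stronger readings that a reader might infer:

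- *That there is no hierarchy at all.* There is one; what is missing is a rule within the secondary tier and a link from it to the primary result.
- *That 90-day mortality is tested without an exploratory label.* It has its own Exploratory outcomes section and is called exploratory again in Appendix 5, although the same 0.05 wording covers it.
- *That the chance of a false secondary result is at least one in four.* That is not a floor. The figure falls below 25 % once the common correlation passes about 0.6, and in the simulation between severity correlations of 0.4 and 0.6.
- *That a promised 5 % rate is exceeded.* The document promises 5 % for the primary outcome and no overall rate for the secondary outcomes.
- *That the chance is near 60 %.* That requires counting the reactions as separate, independent tests (18 tests: 1 − 0.95^18 = 60 %).

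The reply does not remove the explicit rule that every secondary p value below 0.05 is significant, nor the hypothesis that reaches into that tier.

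**Conclusion.** The point holds in limited form. The article declares significance at 0.05 for ten secondary outcomes without an order, a gate or a statement that they are supportive, while its hypothesis includes content measured by two of them. With no true effect, the chance of at least one significant secondary result is roughly 13 to 40 % for ten two-sided tests. The position in that range depends on correlations that the document does not give; the outcome-level simulation gives 16 to 31 % under its own assumptions. Primary inference, sample size and the phase III criterion are unaffected. Priority is low to moderate.

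**What to change.** In Statistical methods and Appendix 5, replace the sentence on significance with: *The confirmatory conclusion rests on the primary outcome alone, tested two-sided at 0.05. Secondary results are supportive, reported as effect estimates with 95 % confidence intervals and p values not adjusted for multiplicity, and are not taken to confirm the hypothesis.*

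Alternatively, if a confirmatory secondary claim is wanted, name a fixed sequence of secondary outcomes to be tested only after a significant primary result. In either case, mark vasopressor use and untoward effects as supportive in the Hypothesis section.

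A ban on secondary p values, or on the word significant, is not needed; for adverse reactions in particular, that would be a reporting preference.

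The cost is wording only: no extra patients, data or change to the sample size. Under the first option, secondary outcomes can no longer be presented as confirmed effects, a minor loss given the stated basis for moving to phase III.
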